**Methods/Design:**

We are conducting an implementation science study using a two-arm cluster site-randomized design to determine the effectiveness of a combination intervention strategy (CIS) using feasible, evidence-based, and practical interventions—including (1) point-of-care (POC) CD4 count testing, (2) accelerated antiretroviral therapy initiation for eligible individuals, and (3) SMS reminders for linkage to and retention in care—as compared to the standard of care (SOC) in Mozambique in improving linkage and retention among adults following HIV diagnosis. A pre-post intervention two-sample design is nested within the CIS arm to assess the incremental effectiveness of the CIS plus financial incentives (CIS + FI) compared to the CIS without FI on study outcomes. Randomization is done at the level of the study site, defined as a primary health facility. Five sites are included from the City of Maputo and five from Inhambane Province. Target enrollment is a total of 2,250 adults: 750 in the SOC arm, 750 in the CIS cohort of the intervention arm and 750 in the CIS + FI cohort of the intervention arm (average of 150 participants per site). Participants are followed for 12 months from time of HIV testing to ascertain a combined endpoint of linkage to care within 1 month after testing and retention in care 12 months from HIV test. Cost-effectiveness analyses of CIS compared to SOC and CIS + FI compared to CIS will also be conducted.

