### Secondary objectives

The secondary objectives include to: 1) evaluate the effectiveness of CIS compared to SOC and the incremental effectiveness of CIS + FI compared to CIS in distinct steps along the HIV care continuum, including linkage to HIV care within 12 months from positive HIV test, retention in care at 12 months from positive HIV test, time from ART eligibility to ART initiation, and disease progression (new World Health Organization [WHO] stage III/IV event, hospitalization, CD4 count, death); 2) evaluate the cost-effectiveness of CIS compared to SOC and the incremental cost-effectiveness of CIS + FI compared to CIS; and 3) assess feasibility and participant acceptability of the relative benefit of the interventions included in CIS and CIS + FI in enhancing linkage and retention.

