#### Participant interviews

Participant interviews are conducted at baseline, and one month and 12 months after study enrollment by study staff using closed-ended questionnaires. The baseline questionnaire collects information on patient socio-demographics, travel to and time spent at the HIV clinic, and HIV testing history. The 1-month and 12-month questionnaires collect information on linkage to care and retention in care. All three questionnaires collect information on quality of life and social support, perceived and experienced HIV stigma, and HIV knowledge and beliefs. Additionally, for patients in the intervention arm, the follow-up interviews assess patient receipt and acceptability of each intervention component. Baseline interviews are completed at the health facility following receipt of informed consent and contact information for follow-up interviews. For the 1-month and 12-month follow-up interviews, study staff makes up to four attempts to reach the participant by phone to complete the interview. If the participant cannot be reached by phone, study staff conducts home visits in an attempt to locate the participant and conduct the interviews. Additionally, participants who are reached by phone and indicate a preference to return to the health facility to complete the interview may do so.

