### Sample size and power analysis

Based on a review of the relevant literature, under the current SOC in Mozambique we conservatively estimated that the combined outcome of linkage within 1 month and retention at 12 months after HIV diagnosis would be 25% (assuming 50% of participants enroll into HIV care within 1 month of diagnosis and 50% of these are retained in care 12 months after diagnosis). We then estimated the minimum difference we could detect in our combined outcome between CIS and SOC arms with 80% power using the Power and Sample Size (Pass 8.0) software for two independent proportions in a cluster randomization study design and a two-sided Farrington & Manning Likelihood Score Test [34], and assuming five study clusters (two sites per cluster) and 300 patients per cluster. With these assumptions, we will have 80% power to detect as statistically significant a relative risk of the combined outcome of linkage and retention between CIS and SOC arms of 1.6 (or an absolute increase in the combined outcome of 20%) comparing the CIS to SOC arms.

To address the objective of comparing the effectiveness of CIS + FI to CIS on the combined outcome of linkage within 1 month of diagnosis and 12 month retention after diagnosis, we are enrolling an additional 150 participants in each of the five CIS sites (total of 750 additional participants in intervention arm) in cohort 3 (CIS + FI) upon completion of enrollment of cohort 2 (CIS). Assuming that the combined outcome of linkage within one month of diagnosis and retention 12 months after diagnosis is 45% in the CIS arm, we will also have greater than 80% power to detect an absolute increase of 21% in the combined outcome comparing CIS + FI to CIS.

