### Statistical methods

To evaluate the effectiveness of CIS as compared to SOC on the combined outcome of linkage to HIV care within 1 month and retention in care at 12 months among adults testing HIV positive.An intent-to-treat analysis will be used to compare the combined outcome of linkage to HIV care within 1 month and retention at 12 months between participants at sites randomized to receive the SOC and participants at sites randomized to receive CIS. We will use multilevel generalized linear regression models to provide statistical estimates controlling for cluster and matched stratum effects. Models will include fixed effects for study condition (treatment arm) and random effects for sites. This approach will take into account the correlation among participants within facilities. In addition, we will compare patient-level and facility-level characteristics hypothesized to influence linkage and retention after data collection has been completed in order to assess whether the randomization evenly distributed important non-matched predictors of linkage and retention between intervention and control arms. Covariates hypothesized to influence linkage and retention that will be analyzed include: actual numbers of adults enrolling in HIV care at each site during the study period, age, gender, baseline measures of CD4 count and WHO stage at enrollment into HIV care, and tuberculosis status at enrollment into HIV care. Should important differences be observed between intervention and control arms, we will additionally conduct covariate-adjusted generalized linear mixed models to assess the degree to which these differences alter our measures of association.To evaluate the incremental effectiveness of CIS + FI compared to CIS on the combined outcome of rapid linkage to HIV care within 1 month and retention in care at 12 months among adults newly diagnosed with HIV.The approach for this objective will follow the approach outlined under objective 1 above; in this case, the combined outcome will be compared between participants enrolling in cohort 3 (receiving CIS + FI) and those enrolling approximately six months earlier in cohort 2 (receiving CIS without FI), all within the same study arm.To evaluate the effectiveness of CIS compared to SOC and the incremental effectiveness of CIS + FI compared to CIS in relation to: linkage to care within one month; retention 12 months after HIV diagnosis; time from eligibility to ART-initiation, and disease progression.Outcomes will be compared under an “intent to treat” scenario and, if significant differences in other determinants of these outcomes are observed between study cohorts at baseline, generalized multilevel mixed models will be used to compare outcomes between study cohorts. In addition, linkage rates and non-retention and mortality rates 12 months after HIV diagnosis will be compared between study arms using Kaplan-Meier survival analytic techniques using robust sandwich estimates to account for clustering. Participants who are lost to follow-up will be censored for mortality and morbidity analyses at the time of last known visit. For the subset of participants determined ART eligible at their site, Cox Proportional Hazards Models will be used to compare the time from ART eligibility to ART initiation between participants receiving CIS + FI, CIS and SOC, censoring participants transferring after ART eligibility but before initiation and treating participants who die before ART initiation as competing risks, and using robust sandwich estimates to account for clustering.To evaluate the cost-effectiveness of CIS compared to SOC and the incremental cost-effectiveness of CIS + FI compared to CIS.The incremental cost-effectiveness ratio is defined as the incremental change in costs divided by the incremental change in effects. This study will use cost-effectiveness to compare SOC with CIS, CIS with CIS + FI, and SOC with CIS + FI. The incremental cost-effectiveness of CIS compared to SOC is equal to the cost of CIS minus the cost of SOC divided by the effectiveness of CIS minus the effectiveness of SOC. In discounting future benefits expected from long-term benefits of the proposed intervention (such as improved life expectancy), we will explore alternative time horizons (ranging from the period of data collection to five years, 10 years, 20 years, and lifetime), and we will use the standard discount rate of 3% for costs and benefits. This discount rate reflects the time preference with regard to costs and benefits (that is, a dollar today is worth more than an inflation-adjusted dollar at some time in the future). The downstream impact of CIS and CIS + FI on future costs and benefits (e.g. the potential impact of prolonging lives) will be included as additional costs and benefits.To assess feasibility and participant acceptability of the interventions included in CIS and CIS + FI in enhancing linkage and retention.To assess feasibility of CIS and CIS + FI, uptake of interventions will be assessed by calculating the proportion of participants reporting that they received each intervention during the 1- and 12-month follow-up interviews and documented within study records as having received them. To assess acceptability, participants are asked to identify whether each intervention was helpful in terms of assisting in timely linkage to care and retention after enrollment into care, the “most useful” and “least useful” intervention, and to identify what aspects of each intervention were useful and not useful. Stratified analyses will examine associations between participant socio-demographic and clinical characteristics and acceptability.

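### Censoring mortality and morbidity at the last known visit probably ties follow-up to retention, which CIS is meant to change, so these secondary comparisons can be biased in either direction

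*Protocol article*

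**What the plan says.** The censoring rule is in the protocol article, Statistical methods, under the third objective: "Participants who are lost to follow-up will be censored for mortality and morbidity analyses at the time of last known visit". The sentence before it says that "mortality rates 12 months after HIV diagnosis will be compared between study arms using Kaplan-Meier survival analytic techniques", with robust sandwich estimates for clustering. The outcomes concerned are listed under Secondary objectives: "disease progression (new World Health Organization [WHO] stage III/IV event, hospitalization, CD4 count, death".

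Three other places bear on how the rule works.

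- The abstract gives a fixed horizon: "Participants are followed for 12 months from time of HIV testing".
- Participant interviews describes study contact outside the clinic: "For the 1-month and 12-month follow-up interviews, study staff makes up to four attempts to reach the participant by phone to complete the interview". It continues: "If the participant cannot be reached by phone, study staff conducts home visits in an attempt to locate the participant". The follow-up questionnaires are said to cover linkage, retention, quality of life, stigma and knowledge. Vital status, date of death and hospitalization are not mentioned.
- Extraction of patient-level data from medical records takes clinical and immunological data from existing electronic patient databases.

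The article does not define *lost to follow-up* or *visit* for these analyses, and nothing connects the censoring date to the 1- and 12-month contacts.

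**The concern.** Kaplan-Meier estimates 12-month mortality without bias only if participants censored at a given time have the same later risk as those still under observation. Clinical data come from clinic records, so the natural reading of *visit* is a clinic visit. A participant who disengages is then censored on leaving care, and one who never links is censored at about the day of the test.

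Retention is half of the primary endpoint and is what CIS is meant to improve, so the amount of follow-up would differ by arm because of the intervention. The Background section says that retention is needed to prevent and treat opportunistic infections and to start ART on time, so people out of care are plausibly at higher risk. Sandwich variances correct standard errors for clustering. They do not correct this bias.

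Morbidity has a related problem. WHO-stage events and CD4 counts recorded in clinic can be seen only while a participant attends. Baseline CD4 is measured at the testing point in CIS sites, but only after linkage and consultation in SOC sites. The better-retained arm has more opportunity to record events.

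What is at stake is the reliability of the mortality and disease-progression comparisons.

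**Working it through.** **Planning figures.** Sample size and power analysis sets SOC by "assuming 50% of participants enroll into HIV care within 1 month of diagnosis and 50% of these are retained in care": 0.50 × 0.50 = 0.25, which reproduces the stated 25%. The assumed CIS value is 45%. The article gives no mortality, loss or tracing rate, so everything below is an illustration.

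**Assumptions.**
- Death hazard per year: h_in = 0.05 in care; h_out = 0.05 to 0.20 out of care.
- SOC: linked share L = 0.50, retained share R = 0.50. CIS: L = 0.675, R = 0.667, so that L × R = 0.45.
- Linked participants leave care at the constant rate μ = −ln R: 0.693 in SOC, 0.405 in CIS.
- Never-linked participants have their last visit at about day 0.
- *Lost* means out of clinic care. q is the share of out-of-care deaths that the study learns of.

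**Observed person-time per participant, in years.** Let A = (1 − e^−(μ + h_in)) / (μ + h_in).
- SOC: A = 0.706, so 0.50 × 0.706 = 0.35.
- CIS: A = 0.803, so 0.675 × 0.803 = 0.54.

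**True 12-month mortality.** (1 − L)(1 − e^−h_out) + L(D_in + D_out), where D_in = h_in × A, D_out = μ(A − e^−h_out × B) and B = (1 − e^−(μ + h_in − h_out)) / (μ + h_in − h_out).

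Example at h_out = 0.15, where 1 − e^−0.15 = 0.1393:
- SOC: 0.50 × 0.1393 + 0.50 × (0.0353 + 0.0391) = 0.107.
- CIS: 0.325 × 0.1393 + 0.675 × (0.0402 + 0.0250) = 0.089.

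**Case (a): out-of-care deaths unknown (q = 0).** Kaplan-Meier sees only the in-care hazard: 1 − e^−0.05 = 4.9% in each arm. The share of deaths counted is L × D_in divided by true mortality.

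| h_out | True SOC | True CIS | Difference (points) | Kaplan-Meier, each arm | SOC deaths counted | CIS deaths counted |
|---|---|---|---|---|---|---|
| 0.05 | 4.9% | 4.9% | 0 | 4.9% | 36% | 56% |
| 0.10 | 7.8% | 6.9% | 0.9 | 4.9% | 22% | 39% |
| 0.15 | 10.7% | 8.9% | 1.8 | 4.9% | 17% | 30% |
| 0.20 | 13.4% | 10.8% | 2.6 | 4.9% | 13% | 25% |

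With equal hazards there is no bias. Otherwise a real difference disappears.

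**Case (b): out-of-care deaths learned through tracing, survivors still cut at their last visit.** Participants who die out of care stay in the risk set until death, while survivors out of care leave it early. Simulation with 400,000 participants per arm and equal hazards of 0.05 (true mortality 4.9% in both arms) gives:
- q = 0.5: Kaplan-Meier 9.0% in SOC, 6.9% in CIS.
- q = 1: Kaplan-Meier 13.0% in SOC, 8.5% in CIS.

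Here a CIS benefit of 2.1 to 4.5 points appears where none exists.

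**The case against.** The strongest reply is that the text does not commit to the harmful reading. It does not say clinic visit, and Participant interviews uses the word for a study contact: "study staff conducts home visits in an attempt to locate the participant and conduct the interviews". If *lost* means not found by the 12-month tracing, a participant out of care but reached at 12 months is not cut early, and the problem is confined to those never found. Operational definitions may also be in the full protocol or the SAP, which are not shown. This stands in part: it makes the size uncertain. The stated rule is still not linked to the study contacts, and the clinic databases as the source of clinical data favour the clinic reading.

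Several stronger inferences are tempting, and the article does not support them.

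- *Everyone is traced at 12 months.* Tracing is attempted. Success is not promised, and recording of deaths is not described.
- *75% of SOC and 55% of CIS are lost.* These are failures of the combined endpoint. They include late linkage, retention at another facility, and death.
- *Half of SOC contribute no follow-up.* The planning value concerns linkage within one month, and some participants link later.
- *The rule necessarily hides a CIS benefit.* Case (b) shows the opposite.
- *The Cox analysis is affected.* Cox models are specified only for time from ART eligibility to initiation, with their own censoring and competing-risk rules.

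Censoring at last known contact is also conventional. It is less safe here because contact with the clinic is itself an outcome of the intervention.

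**Conclusion.** The concern holds on the natural reading of the rule. If the last visit is a clinic visit, censoring depends on retention and is likely to be informative and unequal between arms, with about 0.35 observed person-years per SOC participant against 0.54 per CIS participant. In the illustration the mortality comparison can hide a true gap of 0.9 to 2.6 points or show a false one of 2.1 to 4.5 points, depending on whether out-of-care deaths are learned. These sizes rest on assumed hazards, an assumed CIS split between linkage and retention, and assumed tracing success. There is no bias if hazards are equal and no out-of-care deaths are learned, and little if *lost* means untraced and few are untraced.

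The primary combined endpoint does not use this rule. The point should be fixed before the secondary outcomes are analysed, but it does not threaten the main conclusion of the trial.

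**What to change.** 1. Define *lost to follow-up* for these analyses. For mortality, replace the last known visit with the last date known alive from any source: clinic records and the 1- and 12-month phone and home-visit contacts. Apply the same rule to deaths and survivors, and close follow-up at 12 months from the HIV test.
2. Record vital status and, where applicable, date of death at those contacts, including from whoever is found at a home visit.
3. Report by arm how many participants have known vital status at 12 months. Add a best-case/worst-case bound or another sensitivity analysis for informative censoring.
4. Keep the planned between-arm morbidity comparison, but state that WHO-stage, CD4 and hospitalization events recorded only in clinic are ascertained unequally by arm. Do not treat confirmed survival as absence of events.

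The cost is a small addition to the tracing form, some analysis work and a change of wording. Some participants will remain untraced, which is why step 3 is needed.

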### Study interventions

#### Standard of Care (SOC)

At sites randomized to the SOC arm, patients are managed per current Mozambican Ministry of Health (MOH) guidelines (Table 2). HCT counselors refer patients diagnosed with HIV to attend HIV care services at their preferred health facility as soon as possible. In most cases, patients are verbally referred to the on-site HIV care and treatment clinic. Patients who present to the health facility receptionist to enroll in HIV care are scheduled for an appointment for clinical consultation in the on-site HIV clinic. Following the clinical consultation, patients are sent to the health facility laboratory to have blood drawn for CD4 count testing and baseline laboratory tests. Laboratory tests are processed at the health facility laboratory in four of the five SOC sites, and are sent off-site for processing at the remaining SOC site. Patients are asked to return for another clinical consultation approximately one to two weeks later to review laboratory results, at which point ART eligibility is determined by CD4 count and WHO stage following national guidelines: CD4 count ≤350 cells/μL and/or WHO stage III/IV. Those who are ART eligible receive on average three counseling sessions before initiating treatment. Patients receiving ART are requested to return to the health facility every two weeks for the first month, at two months, at six months, and then every six months thereafter. Patients not eligible for ART are requested to return in six months for clinical evaluation and routine laboratory testing. Peer educators follow-up with patients who miss appointments on ad hoc basis via phone or home visits.

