**Table 2 Tab2:** **Combination intervention strategy interventions compared to standard of care**

Intervention	Standard of care	CIS (CIS, CIS + FI)	Barriers targeted by interventions
**CD4 testing**	CD4 (Cyflow, FACS Caliber/Count, POC CD4) at HIV care site laboratory if linkage completed.	POC CD4 assays at HIV testing points.	Structural
	Turnaround time: 1–4 weeks.	Turnaround time: immediate.	
**Accelerated ART initiation**	Within 1–2 months from linkage.	Accelerated ART initiation within 1 week from testing.	Biomedical
	2-3 counseling sessions, all in HIV care.	2 counseling sessions, one in HCT immediately following POC CD4 test and one in HIV care.	
	Baseline laboratory tests results obtained prior to initiation.	Draw blood for baseline laboratory tests, and initiate prior to results.	
**Cellular appointment reminders**	None.	SMS appointment reminders for all participants.	Behavioral
**Non-cash financial incentives**	None.	Pre-paid cellular air time cards.	Structural

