#### POC CD4 count testing

Patients at the intervention sites receive a POC CD4 count test in the HCT point of service immediately following HIV diagnosis by the HCT counselor. Results are available and provided to the patient along with an explanation of their meaning within 20 minutes. All patients, regardless of CD4 count, are provided with a referral slip for the on-site HIV care clinic and instructed to enroll in care as soon as possible, although particular emphasis on prompt enrollment is provided to patients who are ART eligible as described below. Patients not yet eligible for ART who agree to enroll in HIV care immediately are escorted to the receptionist’s office, whereas those who are ART eligible receive the accelerated ART initiation intervention described below.

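### Comparisons with SOC on time from ART eligibility to ART initiation use a risk set and a time zero that differ by arm, so the hazard ratio understates the CIS benefit

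*Protocol article*

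**What the plan says.** The Secondary objectives section of the protocol article lists "time from ART eligibility to ART initiation" among the steps of the care continuum on which CIS is compared with SOC, and CIS + FI with CIS. Under Statistical methods the analysis set and model are fixed: "For the subset of participants determined ART eligible at their site, Cox Proportional Hazards Models will be used". All three cohorts are set against each other on this interval. Transfers are handled by "censoring participants transferring after ART eligibility but before initiation", deaths before ART are competing risks, and robust standard errors allow for clustering. No rule covers people who were never assessed for eligibility.

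Eligibility is reached differently in the two arms:

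- **SOC.** After enrolling in care, seeing a clinician and having blood drawn, the patient is "asked to return for another clinical consultation approximately one to two weeks later to review laboratory results, at which point ART eligibility is determined". Table 2 places the CD4 count "at HIV care site laboratory if linkage completed" and gives a turnaround of 1–4 weeks.
- **CIS and CIS + FI.** "Patients at the intervention sites receive a POC CD4 count test in the HCT point of service immediately following HIV diagnosis". Table 2 gives the turnaround as immediate. Those with a count of 350 or below are treated as ART eligible from that moment, before they reach the HIV clinic.

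Table 2 also counts its ART timing from different origins: 1–2 months from linkage in SOC, 1 week from testing in CIS.

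**The concern.** Being determined eligible is a status acquired after randomisation, and the intervention changes both who acquires it and when. An eligible person at a CIS site who never links stays in the analysis as a non-initiator. The same person at an SOC site never has a CD4 count and is absent. Those who do enter at SOC sites have already shown that they attend and return, and their waiting time up to the result is not counted.

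This is no longer a comparison of the randomised groups, although the article promises an intent-to-treat comparison for these outcomes. It is also the only listed outcome that times ART initiation; nothing listed measures time from HIV test to ART. The trial could therefore report slower ART initiation under CIS when CIS starts as many people as SOC, or more, and sooner after diagnosis.

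**Working it through.** The article gives no event count, effect size or power for this outcome, so there is no figure to reproduce.

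**Inputs from the article.** SOC linkage: 50% within 1 month (Sample size and power analysis), 57% within 30 days in Mozambique and up to 78% within three months in the region (Background). Initiation among eligible people: 66% (Background). CD4 turnaround: 1–4 weeks in SOC, immediate in CIS (Table 2). Target: 750 per cohort.

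**Assumptions.** Half of those enrolled are eligible by CD4 count; 80–100% of SOC linkers return for the result; the 66% applies to people who link and are identified as eligible.

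**Step 1: who can enter the risk set.** In CIS, everyone eligible by CD4 count at testing: 0.50 × 750 = 375. In SOC, the share of truly eligible people is linkage × return:

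- 50% linkage: 0.50 × 0.80 to 0.50 × 1.00 = 40–50%
- 57% linkage: 46–57%
- 78% linkage: 62–78%

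That is about 150 to 292 of 375 in SOC.

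**Step 2: when the clock starts.** In CIS, on the day of the test. In SOC, after the time to linkage plus the wait for the result.

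**Step 3: a true tie.** Give both arms the same linkage L and 66% initiation among linkers, and let every SOC linker be identified. Of all eligible people, L × 0.66 start ART in each arm. The planned subset shows 0.66 in SOC, because non-linkers are gone, and L × 0.66 in CIS. Under proportional hazards the implied CIS vs SOC hazard ratio is ln(1 − 0.66L) / ln(1 − 0.66):

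| L | True share starting, both arms | Planned subset, SOC vs CIS | Implied HR |
|---|---|---|---|
| 50% | 33% | 66% vs 33% | ln 0.67 / ln 0.34 = 0.37 |
| 57% | 38% | 66% vs 38% | ln 0.624 / ln 0.34 = 0.44 |
| 78% | 51% | 66% vs 51% | ln 0.485 / ln 0.34 = 0.67 |

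With 66% initiation in both arms, CIS would need 100% linkage merely to match the SOC subset proportion.

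**Step 4: adding timing.** A simulation of 20,000 truly eligible people per arm fitted the Cox model as planned and again from the HIV test, to 12 months. It assumed:

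- time to linkage exponential, capped at 30 days, mean 10 days (5 days in CIS in the last four rows);
- SOC turnaround uniform over 7–28 days;
- mean delay to ART of 30 days after eligibility in SOC and, after linkage in CIS, 30 days (first row) or 5 days (other rows);
- full return for results, and no deaths, transfers or clustering.

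A hazard ratio above 1 means faster initiation in CIS.

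| Scenario (SOC to CIS) | HR as planned | HR from test | On ART by 12 months, SOC / CIS |
|---|---|---|---|
| Linkage 50%, initiation 66%, same delay in both | 0.36 | 1.08 | 33% / 33% |
| As above, faster start in CIS | 0.44 | 1.20 | 33% / 33% |
| Linkage 50% to 70%, initiation 66% in both | 0.74 | 1.97 | 33% / 46% |
| Linkage 50% to 80%, initiation 66% to 80% | 1.24 | 3.42 | 33% / 64% |
| Linkage 57% to 80%, initiation 66% to 80% | 1.24 | 2.99 | 38% / 64% |
| Linkage 78% to 90%, initiation 66% to 80% | 1.57 | 2.78 | 51% / 72% |

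The planned hazard ratio is the lower one in all six rows and lies on the wrong side of 1 in three.

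**The case against.** The planned interval is exactly the one named in the objective, as one step among several. That stands: plan and objective agree. A reader might infer that the objective goes unanswered, but the fault lies in choosing this step as a comparison with SOC.

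A reader might also infer that the analysis cannot measure accelerated ART at all. The article does not support that. Expedited consultation, same-day initiation and starting before laboratory results all act after eligibility is known, and the interval observes them, though between differently selected groups. Earlier gains show partly in the linkage outcomes, which run from the HIV test, but those do not time ART.

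Nor is eligibility known on the test day for everyone at CIS sites. National criteria include WHO stage III/IV, and POC testing settles only the CD4 criterion. The gap concerns eligibility by CD4 count.

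The sizes can be challenged. The 50% is a one-month planning value used here for a 12-month outcome, and linkage continues after one month; at 78% the distortion is smaller but remains. The delays and the CIS linkage levels are assumed. Reversal is therefore possible, not established.

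A fuller analysis plan could define the eligibility date more closely, but an SOC patient who never links has no CD4 result to date.

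**Conclusion.** The point holds for CIS vs SOC and for any CIS + FI vs SOC contrast from the same model. The differing risk set and time zero follow from the text alone. The direction, against CIS, follows from non-linkers counting in one arm only and from the omitted SOC delay. The size rests on the assumptions above: planned hazard ratios of 0.36 to 1.57 where the hazard ratio from the test was 1.08 to 3.42.

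Three wider readings are not supported. CIS + FI vs CIS shares the same sites and one POC-based time zero, so this defect largely spares it. The combined primary outcome is counted from the HIV test and is untouched. And because the bias runs against CIS, the danger is a missed or reversed benefit, not a false claim of one.

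**What to change.** For comparisons with SOC, make time from the HIV-positive test (enrolment follows it immediately) to ART initiation within 12 months the comparative outcome in all enrolled participants. Keep non-linkers at risk, treat death before ART as a competing event, as the article already intends, and account for site clustering and matched pair. Report time from eligibility to initiation descriptively for SOC and CIS, and keep it as a comparison for CIS + FI vs CIS.

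This changes a secondary outcome definition as well as its analysis, so it should be recorded as such before outcome data are examined. The article does not list the extracted dates, but the planned Cox model already needs ART dates and enrolment gives the test date, so no new data collection appears necessary.

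The statistical cost is small. Participants not eligible for ART dilute the absolute difference. The ratio of cumulative incidences is preserved only if the eligible share is balanced between arms. That should be checked as far as the data allow, because patients at intervention sites have their CD4 result before they hear about the study.
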